## Eligibility Criteria

### Inclusion Criteria

The participant must meet all of the inclusion criteria to eligible for this study:

1. Be 16-29 years old
2. Being competent and willing to consent to study participation
3. Meets CHR criteria for a psychosis risk syndrome based on the Structured Interview for Psychosis Risk Syndromes (SIPS) either currently or at some point in the past 3 years.

### Exclusion Criteria

An individual who meets any of the following criteria will be excluded from participation in this study:

1. Diagnostic and Statistical Manual of Mental Disorders (DSM-5) diagnosis of psychotic disorder (e.g., schizophrenia spectrum disorder, mood disorder with psychotic features)
2. diagnosis of intellectual disability previously documented in the patient chart
3. Severe developmental disorder
4. Acute suicidality requiring immediate intervention

## Participant Withdrawal Criteria

Participants are advised in the consent form that they are free to withdraw from the study at any time without prejudice and may be withdrawn at the Investigators discretion.

The study participation will also be terminated should participants develop or are found to have any condition that might compromise safety (e.g. unstable vitals) Other reasons for withdrawing individual participants from the study may include one of the following:

- Major protocol violation
- Participant lost to follow-up
- Withdrawal of consent
- Any participant may be discontinued from the study at the discretion of the investigators if it is deemed to be in the best interest of the participant.

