To adapt an existing, effective, validated psychological intervention for use in young people with CHR and offered virtually. Young people with lived experience of psychosis will be engaged to review the OHP materials and work with the team to develop CHR-relevant adaptations, such as examples and vignettes, throughout the intervention package. **H1**: OHP can be clinically adapted and refined in a developmentally appropriate way for virtual use among CHR individuals.

## Specific Aim 2

To evaluate the acceptability of OHP and the feasibility of conducting a clinical trial of OHP in individuals with CHR. **H2:** OHP will be acceptable to CHR individuals as demonstrated by qualitative feedback, attendance rates of OHP sessions and the Client Satisfaction Questionnaire (CSQ). OHP for CHR individuals will be feasible as demonstrated by our ability to recruit our desired sample of 30 participants and retain 80% of those recruited by the end of the 12-week study period. Participants’ ability to complete the clinical assessment schedule will also serve as a feasibility indicator.

## Specific Aim 3

To assess the preliminary efficacy of OHP in enhancing resiliency, reducing depression and anxiety, and improving functioning in individuals with CHR in a single-arm exploratory clinical trial. The design has been informed by the MRC framework of developing complex interventions. **H3:** Individuals with CHR receiving OHP will demonstrate enhanced resiliency, reduced depression and anxiety, and improved functioning as a result of treatment.

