## Quantitative methods

Single arm, pre/post design intervention study. The OHP intervention will be delivered over 12-weeks. Measures will be completed at study entry and repeated immediately post-treatment at 12-weeks. Assessments are clinician rated and will be completed with a trained research assistant.

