# RESEARCH PROCEDURES

## Research Visits

When possible, assessments will be done virtually. Please see schedule of events below. After informed consent has been obtained; participants will complete screening assessments to determine eligibility; followed by baseline clinical, functional and neuropsychological assessments. The clinical, functional and neuropsychological assessments will be repeated approximately 12-weeks (up to 18 weeks after baseline). These assessments can be scheduled on the same day or separate days depending on participant preference. If participants completed overlapping clinical, cognitive or functional assessments as part of their participation of any CAMH study they may be shared, if the participant agrees (based on participant consent). Additionally, many clinics at CAMH use certain rating scales and collect demographic, educational, and cognitive information as part of routine clinical care. For study participants where this information has already been collected as part of routine clinical care, we will endeavor to utilize this already collected information rather than repeating these assessments with participants, if the participant agrees (based on participant consent). Sharing information and assessments will reduce participant burden both by shortening research assessment duration and reducing the stress that can occur with repeated questions on the same topics. Consent for this will be obtained as part of the informed consent procedures for this study.

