**Functioning**

1. The Self-report World Health Organization - Disability Assessment Schedule (WHO-DAS 2.0, self and proxy versions) - a 12-item generic assessment instrument for health and disability ^[34]^. This tool produces standardized disability levels and profiles directly linked at the level of the concepts to the International Classification of Functioning, Disability and Health (ICF), and covers six domains of functioning: cognition, mobility, self-care, getting along, life activities, and participation. Can be administered virtually. [5 minutes to complete]
2. Global Functioning: Social and Role Scales - brief clinician-administered measures of social and role functioning, respectively, administered as a semi-structured interview with detailed anchors for ratings that address functional difficulties typically experienced by youth with subsyndromal PSS ^[33]^. Can be administered virtually. [10 minutes to complete]

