# STATISTICAL PLAN

## Sample Size Determination

There will be 30 participants enrolled in this 12-week single-arm trial. We aim to recruit 30 participants to account for 20% loss to follow up ^[39]^. The sample size was informed by published literature, which suggests 24-50 participants for feasibility trials ^[36]^ ^[37]^. The proposed sample size will provide reasonably reliable quantitative estimates for the targeted feasibility measures. The margins of error are ±12.7% for recruitment rate, ±14.3% for adherence/retention/attrition, and ±12.0% for completeness of outcomes. For Aim 3, the minimum detectable effect size for a pre-post test is 0.60 (Cohen’s D).

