## Statistical Methods

Data will be analyzed principally using descriptive statistics to assess rates of recruitment, retention, intervention fidelity, and treatment response. Distributional characteristics of the outcome measures will be assessed for ceiling and floor effects and rates and patterns of missing values. The primary trial outcome will be impact of OHP on functioning, via the Global Functioning: Social and Role Scales. Our prior work with youth has informed us that functioning is more relevant to them than symptom severity ^[40]^. All participants will be assessed at baseline and study completion. The analysis will run a pre-post test to assess for any significant improvements following intervention; given the small sample size, appropriate to a feasibility trial, we will also calculate effect sizes (Cohen’s *d*), which we will compare with the effect sizes from previous OHP trials to gain a sense of the effect that might be achieved in the full-scale trial.

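### The safety and discretionary withdrawal rule ends study participation, not only OHP, and schedules no outcome assessment afterwards; if such cases occur and change less favourably than completers, the pre-post Cohen's d is somewhat overstated

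*Protocol*

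**What the plan says.** Under Participant Withdrawal Criteria, the protocol says "The study participation will also be terminated should participants develop or are found to have any condition that might compromise safety", with unstable vital signs as the only example. It adds "Any participant may be discontinued from the study at the discretion of the investigators" where this is judged best for the participant. Both rules act on the study as a whole. Neither mentions stopping the intervention while keeping the assessment.

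Outcome timing is set under Quantitative methods: "Measures will be completed at study entry and repeated immediately post-treatment at 12-weeks". Research Visits widens the window: "The clinical, functional and neuropsychological assessments will be repeated approximately 12-weeks (up to 18 weeks after baseline"). The Schedule of Events shows one follow-up column and no early-termination visit. Research Visits also lets overlapping assessments from other CAMH studies or routine care be shared, if the participant consents.

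Statistical Methods names functioning, measured by the Global Functioning: Social and Role Scales, as the primary trial outcome. It plans a pre-post test and Cohen's d, to be set beside earlier OHP trials "to gain a sense of the effect that might be achieved in the full-scale trial".

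**The concern.** A rule that removes people for safety reasons can select on outcome. If those removed would have changed less favourably, the remaining pairs give too large a mean change and too small a spread, and both push d upwards. What matters is the change from baseline: a participant with low functioning throughout, but the same change as completers, would not bias the mean change.

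The issue belongs in the protocol. An SAP can choose how to treat missing scores, but it cannot recover scores that the withdrawal rule stops being collected. In a single-arm trial no control group would reveal the selection. At stake is how well d serves as a rough guide for planning the full-scale trial.

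**Working it through.** **1. The plan's own figure.** Sample Size Determination says "the minimum detectable effect size for a pre-post test is 0.60", with 30 enrolled and 20% loss. Evaluable n = 30 × 0.80 = 24. Significance level and power are not stated; I assume two-sided 0.05 and 80%. A paired t-test (noncentral t) at n = 24 then gives a minimum detectable d of 0.597, and power at d = 0.60 is 80.4%. With all 30 evaluable it would be 0.529. So 0.60 fits an analysis of 24 participants with both scores.

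**2. Inputs for the illustration.** The documents give neither a 12-week rate of safety or discretionary terminations nor an expected change in those terminated. Assumed values:
- completers: mean change 0.60 and SD 1, so d = 0.60 (borrowed from the detectable effect, not a forecast);
- d = mean change divided by the SD of the changes;
- all other losses change like completers;
- k of 30 are terminated under the rule and unassessed, with mean change −c and SD 1;
- c = 0 (no change) or c = 1 (worse by one SD).

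**3. Formula.** With p = k/30, for all 30:

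mean = ((30 − k) × 0.60 − k × c) / 30

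SD = √(1 + p(1 − p)(0.60 + c)²)

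d = mean / SD

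**4. Results.**

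| k | c | mean | SD | d, all 30 | overstatement by completers' 0.60 |
| --- | --- | --- | --- | --- | --- |
| 0 | – | 0.600 | 1.000 | 0.600 | 0 |
| 1 | 0 | 0.580 | 1.006 | 0.577 | 0.023 |
| 1 | 1 | 0.547 | 1.040 | 0.525 | 0.075 |
| 2 | 0 | 0.560 | 1.011 | 0.554 | 0.046 |
| 2 | 1 | 0.493 | 1.077 | 0.458 | 0.142 |

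If those terminated change exactly as completers do, the overstatement is zero for any k.

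**5. Against sampling error.** At n = 24 and d = 0.60, SE = √(1/24 + 0.36/48) = 0.222. The approximate 95% interval is 0.60 ± 1.96 × 0.222, or 0.17 to 1.03. Every shift in the table is smaller than one standard error. Under the stated condition, though, the shift always goes the same way.

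**6. What the fix could recover.** Take k = 2 and c = 1, with one of the two attending. Then 28 changes average 0.60 and one is −1: mean = (16.8 − 1)/29 = 0.545, SD = √(1 + (1/29)(28/29)(1.6)²) = 1.042, d = 0.523. That compares with 0.60 if neither is assessed and 0.458 if both are.

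**The case against.** The strongest reply is that the protocol nowhere says a follow-up score will be withheld after a safety termination. Target Population and Statistical Methods both say that all participants will be assessed, and scores may be shared from routine care or another study. This stands in part: the gap is inferred. But those general statements make no provision for someone whose participation has ended, sharing depends on consent and on a suitable assessment existing, and adverse event follow-up does not cover the outcome scales. The commitment that no new data are collected, under Participant Recruitment and Screening, concerns people who leave by their own choice, so it does not settle the matter.

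The second reply is that there may be no such cases. This stands. The one named trigger is somatic, Risks/Benefits anticipates no risks from a light-touch programme, and acute suicidality is excluded at entry. A reader might infer that psychiatric crises will trigger the rule, since the Background cites lifetime risks of 49% for self-harm and 18% for attempted suicide. Those figures give no 12-week rate. For acute psychosis or suicide risk, Risks/Benefits prescribes help in reaching care and says nothing of termination. Such cases could fall under the open wording, but this is not stated. Participants whose functioning declines without a safety concern stay in and are assessed.

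Third, little rests on d: Aim 3 is exploratory and the analysis mainly descriptive. This also stands and limits the severity.

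A reader might also infer that the rule distorts the feasibility aim to "retain 80% of those recruited by the end of the 12-week study period". It does not. Someone whose participation had to be ended was not retained, and counting that as a loss is an honest feasibility result.

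Finally, a remedy confining study withdrawal to withdrawn consent or loss to follow-up would take away the investigator's power to end assessments for a participant's own good. That objection is right, and the fix below keeps the power.

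**Conclusion.** The point holds as a conditional one of low severity. As worded, the rule ends study participation and leaves no planned follow-up Global Functioning score for those stopped. If any are stopped, go unassessed and change less favourably than completers, d is overstated: by 0.02 to 0.14 for one or two cases among 30, given a completer d of 0.60 and a change in those stopped of between none and one SD worse. That is below the standard error of about 0.22.

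A reader might conclude that the trial's effect size will be inflated. The documents do not support this: they give no rate of such terminations and no direction of change in those affected, and with no cases the effect is nil. What justifies a change is that the lost scores cannot be recovered later and prevention costs very little.

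**What to change.** In Participant Withdrawal Criteria, make stopping OHP the default when a safety concern or investigator judgement requires action. Add that, with consent and where clinically safe, these participants are offered the follow-up visit within the existing window of up to 18 weeks after baseline, at least for the Global Functioning scales. The protocol describes these as "Can be administered virtually. [10 minutes to complete"]. Include the scores in the pre-post estimate and record the reason for stopping. Keep the investigator's power to end all participation, assessments included, in the participant's best interest.

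The cost is two or three sentences, matching consent wording, and about 10 minutes for each participant stopped, probably a few people at most. Recovery will be partial, because some acutely unwell participants will not attend.

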# RESEARCH PROCEDURES

## Research Visits

When possible, assessments will be done virtually. Please see schedule of events below. After informed consent has been obtained; participants will complete screening assessments to determine eligibility; followed by baseline clinical, functional and neuropsychological assessments. The clinical, functional and neuropsychological assessments will be repeated approximately 12-weeks (up to 18 weeks after baseline). These assessments can be scheduled on the same day or separate days depending on participant preference. If participants completed overlapping clinical, cognitive or functional assessments as part of their participation of any CAMH study they may be shared, if the participant agrees (based on participant consent). Additionally, many clinics at CAMH use certain rating scales and collect demographic, educational, and cognitive information as part of routine clinical care. For study participants where this information has already been collected as part of routine clinical care, we will endeavor to utilize this already collected information rather than repeating these assessments with participants, if the participant agrees (based on participant consent). Sharing information and assessments will reduce participant burden both by shortening research assessment duration and reducing the stress that can occur with repeated questions on the same topics. Consent for this will be obtained as part of the informed consent procedures for this study.

**Clinical Assessments**

To reduce participant burden, where possible clinical assessments will not be repeated if administered in another study (as outlined above).

**Categorical Assessments**

The Structured Clinical Interview for DSM-5 (SCID-5) ^[32]^ will be used for all participants. The SCID is a semi-structured diagnostic interview designed to assist clinicians, researchers, and trainees in making reliable DSM-5 psychiatric diagnoses. Can be administered virtually. [Approximately 60-120 minutes to complete]

**Dimensional Assessments**

**Psychosis Symptoms**

1. All participants will be administered the PRIME-Revised ^[27]^. This assessment is harmonized with existing measures already utilized in several studies and clinical services at CAMH to minimize participant/patient burden [5 minutes to complete].
2. CHR participants will be administered the Structured Interview for Prodromal Symptoms (SIPS) ^[26]^: The SIPS is a widely used structured interview for diagnosing a CHR syndrome for psychosis and cases of first episode psychosis. It contains a severity rating scale (the Scale Of Psychosis-risk Symptoms, or SOPS), a well-anchored Global Assessment of Functioning (GAF), the DSM-IV schizotypal personality disorder checklist, a brief assessment of the family history of psychosis, and the Criteria Of Psychosis-risk Syndromes (COPS) and Presence Of Psychosis Scale (POPS) and DSM-5 Attenuated Psychosis Syndrome criterion sets. The SIPS rules in/out the current and lifetime presence of psychosis and when psychosis has never been present diagnoses three CHR syndromes. Can be administered virtually. [120 minutes to complete]

**Mood Symptoms**

1. Calgary Depression Scale for Schizophrenia (CDSS)^[28]^ measures the severity of depression symptoms. It is of a 4-point likert type scale with nine items with higher score indicating higher severity. Analyses resulted in a final set of of 9 diagnostic items; each item is accompanied by a brief description. Items are rated on a 4-point scale ranging from 0 (Absent) to 3 (Severe). Survey administration can be done virtually. [5 minutes to complete]

**Anxiety Symptoms**

1. The State-Trait Anxiety Inventory (STAI)[^29]^ is a commonly used measure of trait and state anxiety. It has 20 items for assessing trait anxiety and 20 for state anxiety. All items are rated on a 4-point scale Higher scores indicate greater anxiety. Survey administration can be done virtually. [5 minutes to complete]

**Functioning**

1. The Self-report World Health Organization - Disability Assessment Schedule (WHO-DAS 2.0, self and proxy versions) - a 12-item generic assessment instrument for health and disability ^[34]^. This tool produces standardized disability levels and profiles directly linked at the level of the concepts to the International Classification of Functioning, Disability and Health (ICF), and covers six domains of functioning: cognition, mobility, self-care, getting along, life activities, and participation. Can be administered virtually. [5 minutes to complete]
2. Global Functioning: Social and Role Scales - brief clinician-administered measures of social and role functioning, respectively, administered as a semi-structured interview with detailed anchors for ratings that address functional difficulties typically experienced by youth with subsyndromal PSS ^[33]^. Can be administered virtually. [10 minutes to complete]

**Cognition**

1. The MATRICS Consensus Cognitive Battery (MCCB) (is intended to provide a relatively brief evaluation of key cognitive domains relevant to schizophrenia and related disorders. The MCCB includes ten tests that assess seven cognitive domains: (1) Speed of Processing; (2) Attention/Vigilance; (3) Working Memory; (4) Verbal Learning; (5) Visual Learning; (6) Reasoning and Problem Solving; and (7) Social Cognition. Requires in person administration for standardization. [60 minutes to complete]

**Resiliency**

1. The Connor-Davidson Resilience Scale (CD-RISC) ^[25]^ This is 25-item self-report rating scale designed to assess resilience, with higher scores being an indicator of high resilience. Each item is rated on a 5-point scale ranging from not true at all or zero to true nearly all of the time or four. The total possible scores range from 0–100. [10 minutes to complete]

## Schedule of Events

| **Procedures** | Screening | Baseline | OHP Intervention (12 weeks) | Follow up Visit |
| --- | --- | --- | --- | --- |
| Informed consent | X |  |  |  |
| Inclusion/Exclusion Determination | X |  |  |  |
| SCID for the DSM-5 | X |  |  |  |
| Connor-Davidson Resilience Scale |  | X |  | X |
| SIPS | X |  |  | X |
| Prevention through Risk Identification, Management and Education Screen – Revised |  | X |  | X |
| Calgary Depression Scale for Schizophrenia |  | X |  | X |
| The State-Trait Anxiety Inventory |  | X |  | X |
| Global Functioning: Social and Role Scales |  | X |  | X |
| WHO-DAS 2.0 |  | X |  | X |
| MATRICS Consensus Cognitive Battery (MCCB) |  | X |  | X |
| Optimal Health Program |  |  | X |  |
| Complete Case Report Forms (CRFs) | X | X | X | X |
| Client Satisfaction Questionnaire |  |  |  | X |
| Adverse Event Log | X | X | X | X |

# STATISTICAL PLAN

## Sample Size Determination

There will be 30 participants enrolled in this 12-week single-arm trial. We aim to recruit 30 participants to account for 20% loss to follow up ^[39]^. The sample size was informed by published literature, which suggests 24-50 participants for feasibility trials ^[36]^ ^[37]^. The proposed sample size will provide reasonably reliable quantitative estimates for the targeted feasibility measures. The margins of error are ±12.7% for recruitment rate, ±14.3% for adherence/retention/attrition, and ±12.0% for completeness of outcomes. For Aim 3, the minimum detectable effect size for a pre-post test is 0.60 (Cohen’s D).

## Statistical Methods

Data will be analyzed principally using descriptive statistics to assess rates of recruitment, retention, intervention fidelity, and treatment response. Distributional characteristics of the outcome measures will be assessed for ceiling and floor effects and rates and patterns of missing values. The primary trial outcome will be impact of OHP on functioning, via the Global Functioning: Social and Role Scales. Our prior work with youth has informed us that functioning is more relevant to them than symptom severity ^[40]^. All participants will be assessed at baseline and study completion. The analysis will run a pre-post test to assess for any significant improvements following intervention; given the small sample size, appropriate to a feasibility trial, we will also calculate effect sizes (Cohen’s *d*), which we will compare with the effect sizes from previous OHP trials to gain a sense of the effect that might be achieved in the full-scale trial.

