## Clinical Data to Date

We have demonstrated the feasibility of OHP in both a completed trial in a community mental health setting ^[16]^ and our ongoing trials across major chronic diseases. In addition, we have built a virtual version of OHP through a web-based portal (optimized for smart phones/tablets) at CAMH which we will use in this study, however, will adapt the content for the CHR population.

**OHP in a community mental health setting in Australia** ^[16]^

Participants with a diagnosed mental illness receiving treatment from an adult mental health service (*n*=92) were followed for 12 months from initiation of OHP. OHP delivered in a community mental health setting demonstrated significant improvements in health and social functioning and reduced hospital admissions and emergency contacts, with net cost savings per patient.

**KOHP: Kidney Disease Optimal Health Program** ^[17]^

Participants with stage 4 or 5 chronic kidney disease (n=57) were followed over a 12-month period from initiation of OHP. At 12-month follow up, the patients who completed the OHP intervention demonstrated significantly decreased depression compared to the usual care group. The results of the pilot evaluation provide support for the efficacy of the OHP intervention in significantly improving depressive symptoms in patients with an established chronic physical illness. It also demonstrated how OHP can effectively address mental health and physical health issues simultaneously.

**MINDS: The Mental Health in Diabetes Service** ^[18]^

Participants with Diabetes Mellitus (*n*=72) were followed over a 6-month period from initiation of OHP. At 3 and 6-month follow up participants in the OHP group showed a significant improvement in quality of life and a significant decrease in anxiety at the 3-month follow up.

Our pilot studies on OHP for different health conditions have demonstrated feasibility in terms of recruitment, acceptability, and implementation. Participants were drawn from metropolitan and rural areas, demonstrating that OHP can be effectively delivered to diverse communities. These initial findings suggest that OHP has the potential to address depression and anxiety symptoms, whilst improving quality of life. However, OHP has never been adapted and applied to a CHR population.

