# Study Objectives

Conventional CHR intervention studies have focused on transition to psychosis, psychosis-like symptoms, and associated distress with little emphasis on functional outcomes. However, given high rates of psychiatric co-morbidity and poor psychosocial functioning in this population it is critical to identify interventions that reduce distress and disability in young people with CHR. Stress-vulnerability models of psychiatric disorders have led researchers to investigate the role of resiliency as a protective factor in maintaining mental health and well-being. Individuals with CHR have lower resiliency scores when compared to healthy controls, and reduced resiliency in the CHR population is associated with anxiety, depression, and poorer functioning. Enhanced resiliency in individuals with schizophrenia is associated with psychosis symptom remission; however, resilience-building interventions for CHR individuals are yet to be established. The current proposal aims to adapt an existing comprehensive resilience-building psychosocial and mental health support program, the Optimal Health Program (OHP), to a CHR population and collect feasibility evidence for a trial testing its ability to improve functioning, reduce distress, and increase resiliency in individuals with CHR. The OHP is a self-management program, which provides a framework to address the psychosocial and mental health needs of individuals, adopting a person-centred approach that empowers the individual to be at the centre of their own health management, and will be offered virtually. OHP has been associated with improved health and functioning and reduced health care costs in adult mental health service users. OHP could greatly impact the long-term mental health, well-being and functioning of CHR youth; however, the feasibility and preliminary efficacy of delivering an intervention tailored around the varied needs of the CHR group must be established before a larger-scale appropriately powered study is pursued. In accordance with the Strategy for Patient-Oriented Research (SPOR), and the Medical Research Council (MRC) framework for developing and evaluating complex interventions, young people with lived experience will be engaged in the study, from co-design of the study and intervention adaptations, through to knowledge translation.

## Specific Aim 1

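### The single-arm pre-post Cohen's d includes untreated change, so comparing it with effect sizes from earlier controlled OHP studies can mix within-arm and between-arm effects and may overstate what a controlled full-scale trial would show

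*Protocol*

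**What the plan says.** Under Quantitative methods the design is a "Single arm, pre/post design intervention study", with measures at entry and at 12 weeks. For the efficacy aim, Statistical Methods states: "The analysis will run a pre-post test to assess for any significant improvements following intervention". It names the Global Functioning: Social and Role Scales as the primary trial outcome and adds a Cohen's d meant to inform the full-scale trial: "which we will compare with the effect sizes from previous OHP trials to gain a sense of the effect that might be achieved". Study Objectives places the present study "before a larger-scale appropriately powered study is pursued".

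Sample Size Determination gives the planning figure: "the minimum detectable effect size for a pre-post test is 0.60", called Cohen's d, with no statement of which SD standardises it.

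Clinical Data to Date summarises three earlier OHP studies. The kidney study reports "significantly decreased depression compared to the usual care group" at 12 months. The community mental health study reports better health and social functioning over 12 months. The diabetes study reports better quality of life at 3 and 6 months and lower anxiety at 3 months. In the reference list, the community study is titled a controlled clinical trial, and the papers cited for the kidney and diabetes programmes are titled as randomised trial protocols. No effect size is given for any of the three.

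The Background expects about a third of people with CHR to remit without treatment.

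**The concern.** A one-arm pre-post d measures everything that changes between entry and 12 weeks. In help-seeking young people that includes natural remission, regression to the mean and whatever care they receive alongside OHP. A controlled effect size subtracts the change seen in the control arm. This d cannot.

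The protocol does not say whether the earlier effect sizes will be within-arm or between-arm. It also does not say how d is standardised or how untreated change will be allowed for. If between-arm effects are taken, as the wording of the kidney result invites, unlike quantities are set side by side. If within-arm changes are taken, the comparison is like with like, but it still does not show what a controlled trial would find.

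At stake is the purpose the protocol itself gives for the comparison, which is a view of the effect in the full-scale trial. If that trial is controlled, the view may be too favourable.

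**Working it through.** **Inputs from the protocol.** "There will be 30 participants enrolled in this 12-week single-arm trial". "We aim to recruit 30 participants to account for 20% loss to follow up". Detectable effect 0.60 for a pre-post test.

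**Inputs assumed.** Two-sided alpha 0.05 and 80% power (neither is stated); pre-post correlation r; equal SD at baseline and 12 weeks; size of untreated change.

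**1. Reproduce 0.60.** Expected completers: 30 × (1 − 0.20) = 24. For a paired t-test, the noncentrality is d_z × √24 with 23 degrees of freedom, where d_z = mean change / SD of change. Solving for 80% power gives d_z = 0.597, which rounds to the stated 0.60. Power at exactly 0.60 is 80.4%. With all 30 participants the result would be 0.529. So 0.60 is a sound figure, on the scale of the SD of change.

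**2. Put it on a raw-SD scale.** With equal SDs, SD of change = SD × √(2(1 − r)), so d_raw = d_z × √(2(1 − r)). Subtracting untreated change c, in raw-SD units, gives the controlled difference that d_z = 0.60 would imply:

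| r (assumed) | d_raw (c = 0) | c = 0.2 | c = 0.3 |
|---|---|---|---|
| 0.3 | 0.71 | 0.51 | 0.41 |
| 0.5 | 0.60 | 0.40 | 0.30 |
| 0.7 | 0.46 | 0.26 | 0.16 |
| 0.8 | 0.38 | 0.18 | 0.08 |

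The standardiser alone can move the value up (r below 0.5) or down (r above 0.5). Untreated improvement only moves it down. At r = 0.3, d_z of 0.60 overstates the controlled difference only when c exceeds 0.71 − 0.60 = 0.11.

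**3. Precision.** An observed d_z of 0.60 with n = 24 has a 95% CI of 0.16 to 1.03 (inversion of the noncentral t).

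**4. Illustration of the consequence.** Two-sample t-test, two-sided 0.05, 80% power:
- Planned on 0.60: 45 per arm.
- True controlled difference 0.40: 45 per arm gives 47% power; 100 per arm would be needed.
- True controlled difference 0.30: 45 per arm gives 29% power; 176 per arm would be needed.

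The 0.40 and 0.30 are the r = 0.5 row of the table with c = 0.2 and c = 0.3. They are not estimates from the protocol.

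**The case against.** - **Between-arm comparators are not established.** A reader might infer that every earlier effect size is between-group, so that the two quantities necessarily differ. The documents do not support that. No earlier effect size is given, only the kidney result is worded as a contrast, and the community and diabetes summaries can be read as change within the OHP group. A controlled trial also yields within-arm change. What stands is that the comparator is left open and mixing is possible.
- **The planning consequence is inferred.** A reader might also infer that the next trial will be sized on this d and will be underpowered. The protocol speaks only of gaining a sense of the effect and does not state the next trial's design. Earlier controlled results could temper an optimistic pilot value as easily as support it. The power figures are therefore illustrative.
- **The bias need not run upwards.** At low pre-post correlation the SD-of-change scale understates a raw-SD d. The remission figure has no 12-week time frame and does not concern the Global Functioning scales. Eligibility sets no functioning threshold, so the amount of regression to the mean is unknown. This limits the claim to possible overstatement.
- **Some comparisons do match.** Depression, anxiety and functioning are also aims here, and the diabetes anxiety result is at 3 months. This is fair, and it is a reason to name those comparisons.
- **Standardisation may belong in the SAP.** The choice of SD alone could be left there. The comparison and its purpose are fixed in the protocol, and that is where the difficulty lies.

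**Conclusion.** The point holds in limited form. The protocol fixes a comparison between a pre-post d that includes untreated change and earlier effects of unspecified type, at least one of them reported against usual care. As a guide to a controlled full-scale effect this is unsound as written and may be too favourable.

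The size cannot be fixed from the documents, because it depends on the pre-post correlation and the untreated change, and neither is given. Over the assumed ranges, d_z = 0.60 corresponds to a controlled difference anywhere from 0.71 (r = 0.3, no untreated change) to 0.08 (r = 0.8, untreated change 0.3 SD). The planning figure of 0.60 is correct and needs only a label. The feasibility and acceptability aims are unaffected. The change should be made, but the trial does not depend on it.

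**What to change.** In Statistical Methods, replace the comparison clause so that it does three things:
1. Reports the mean change, the SD of change, the pre-post correlation, and the change divided by baseline SD with its 95% CI.
2. Limits the comparison to within-arm OHP changes from earlier studies, in the same outcome domain and at the nearest time point.
3. States that the pre-post d includes untreated change and will not be taken as the effect expected in a controlled full-scale trial.

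In Sample Size Determination, label 0.60 as mean change divided by the SD of change.

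The cost is a few extra summary statistics from data already scheduled, with no added participants or visits. The downside is a less favourable reading of the pilot effect, and fewer earlier results may qualify for comparison.
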